### 3.7. Statistical Analysis

All analyses will be performed using SPSS v.25 (SPSS, Inc., Chicago, IL, USA). Missing data will be handled by intention-to-treat analysis (multiple imputation method). The description will be made as measures of central tendency and dispersion (continuous variables) and as percentages (categorical variables). Using the Shapiro–Wilk test, the normality of the data will be verified, and a two-step rank transformation will be applied to the non-normal variables. Homoscedasticity will be analyzed using Levene’s test. A 2-way repeated measures analysis of variance (ANOVA) will be used to determine the effects of the interventions. The effects of the model are the group (GE1; GE2; GC), the times (pre-test; post-test), and their interaction over time (time × group). Bonferroni’s post hoc test will be applied to identify statistically significant comparisons. The effect size will be determined using Cohen’s d (<0.2 insignificant; ≥0.2 and ≤0.49 small; ≥0.5 and ≤0.79 moderate; ≥0.8 large), considering *p* < 0.05 and GraphPad Prism v8.

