To analyze the effects of a combined program of resistance exercises, nutritional recommendations, sleep, and use of screens in schoolchildren from educational establishments in Punta Arenas.

*Specific objectives (SO)*

**SO1:** To determine the physical condition, cardiovascular risk, and lifestyles at the beginning and at the end of the respective interventions in experimental group 1 (group that will carry out a combined program of muscular strength exercises and nutritional and lifestyle education related to sleep and use of screens), experimental group 2 (group that will carry out nutritional education and lifestyle activities related to sleep habits and use of screens), and the control group (group that will carry out the usual school day concerning physical education classes).

**SO2:** To compare the groups (intragroup differences) and between the groups (intergroup differences) in physical condition, cardiovascular risk, and lifestyles after both interventions.

**SO3:** To determine the benefits of the intervention of experimental group 1 in physical condition, cardiovascular risk, and lifestyles that allow making relevant and evidence-based decisions on the health of schoolchildren.

The following research hypotheses (Rh) are proposed:

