**Rh1:** 
*A combined program of muscular strength exercises and nutritional education improves the physical condition, cardiovascular risk, and lifestyles of schoolchildren from educational establishments in Punta Arenas.*

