### 2.2. Participants

The participants will be students of the 2nd formative cycle (fifth basic year) from two educational establishments in the commune of Punta Arenas, Magallanes Region, Chile. The ages selected for the research correspond to the highest percentage of schoolchildren with obesity and overweight in the region. The sample size will be 144 children (48 for intervention group 1, 48 for the intervention group 2, and 48 for the control group), which was obtained considering 50% heterogeneity, a margin of error of 5%, and a level of 95% confidence. The sample size was calculated a priori using G*Power 3.1.9.7. A total of 132 participants are required (22 in each course) considering α = 0.05, 1-β = 0.8, and an effect size of (ES) = 0.8. Considering the possibility of dropout, 12 more people were added (total *n* = 144; *n* = 24 in each course).

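### Pre-to-post change within an arm could be read as a programme effect (SO2, Rh1); the planned time × group test avoids this but is less precise than baseline-adjusted ANCOVA

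*Protocol article*

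**What the plan says.** Section 3.7 (Statistical Analysis) gives the model: "A 2-way repeated measures analysis of variance (ANOVA) will be used to determine the effects of the interventions". Its terms are group, time and their interaction, followed by Bonferroni post hoc comparisons. No baseline-adjusted model is mentioned.

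Two statements in section 1 (Introduction) bear on how the results will be read. SO2 sets out "To compare the groups (intragroup differences) and between the groups (intergroup differences", so change within an arm is an objective next to the contrast between arms. Rh1 reads "A combined program of muscular strength exercises and nutritional education improves the physical condition, cardiovascular risk, and lifestyles" and names no comparator. Rh2 does name its comparators: education alone and the usual school day.

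The pre-test is planned in all three groups (section 3.3) and every outcome is measured before and after the intervention (section 3.6.3). Table 2 puts the pre-test in March and the post-test in October/November. The control group runs concurrently (section 3.5.1). Six courses are randomised, two per arm (section 3.4).

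**The concern.** Children aged 10 to 12 grow, the season changes, and a repeated test may be done better the second time. The article itself treats strength as age-dependent: section 3.6.2 uses reference values defined by age and sex. A pre-to-post test in one arm cannot separate these influences from the programme. Because Rh2 already covers the contrasts with education alone and with usual school, Rh1 invites reading as a within-arm claim. It could then be declared confirmed although the programme did nothing.

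The second matter is precision. The interaction in section 3.7 is a valid between-arm comparison, but with two time points it compares change scores. The planned pre-test would be better used as a covariate.

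**Working it through.** **Inputs from the article.** Section 2.2: "A total of 132 participants are required (22 in each course", hence 2 × 22 = 44 evaluable children per arm; 12 are added for dropout, giving 144, or 48 per arm. The significance level is 0.05. The article gives no figure for this point that could be reproduced. Whether 132 follows from its stated inputs is a separate question on which nothing here depends.

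**Assumptions.** The article gives no SD, no pre-post correlation r and no expected change without the programme. I work in SD units with r from 0.5 to 0.9 and a shared change g of 0.1 to 0.3 SD.

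**Step 1: within-arm test, no programme effect.** The SD of a change is √(2(1−r)), so the paired test has noncentrality g·√44 / √(2(1−r)). For g = 0.3 and r = 0.8 this is 0.3 × 6.633 / 0.632 = 3.15. Two-sided rejection probabilities from the noncentral t with 43 df:

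| Shared change | r = 0.5 | r = 0.8 |
|---|---|---|
| 0.1 SD | 10% | 18% |
| 0.2 SD | 25% | 54% |
| 0.3 SD | 49% | 87% |

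**Step 2: time × group under the same conditions.** In 4,000 simulated trials with g = 0.3 SD in every arm and no effect, the interaction rejects in 4.7% (r = 0.8) and 5.0% (r = 0.5), with a mean estimate of 0.00. The control arm shares the change, so it cancels.

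**Step 3: precision, treating children as independent.** Residual variance is 2(1−r) for the change score and 1−r² for ANCOVA. The ratio is (1−r²) / (2(1−r)) = (1+r)/2. The standard error of a pairwise difference is √(2 × variance / 44).

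| r | Variance ratio | SE, change score | SE, ANCOVA | Power for 0.3 SD, change score | Power for 0.3 SD, ANCOVA |
|---|---|---|---|---|---|
| 0.5 | 0.75 | 0.213 | 0.185 | 29% | 37% |
| 0.8 | 0.90 | 0.135 | 0.128 | 60% | 65% |
| 0.9 | 0.95 | 0.095 | 0.093 | 88% | 90% |

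**Step 4: the main effects.** The time effect measures change common to all arms. The group effect averages pre-test and post-test, so a post-test difference of 0.3 SD enters it as 0.3/2 = 0.15 SD. With a true 0.3 SD effect and r = 0.8, simulated omnibus power is 10.5% for the group effect, 61% for time × group and 66% for ANCOVA.

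**Step 5: courses.** With an assumed course-level variance of 0.02 SD², r = 0.8 and no effect, child-level analyses reject in 23% (time × group) and 25% (ANCOVA) of trials. The simulated standard errors are 0.1989 and 0.1945, a variance ratio of 0.1945² / 0.1989² = 0.956 rather than 0.90. ANCOVA leaves the course error in place, and that error dilutes the gain.

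**The case against.** The strongest reply is that the plan already contains the right test. A reader might infer that the repeated-measures ANOVA itself credits growth and season to the programme. The article does not support that: the interaction is in the model, the control arm is concurrent, and step 2 shows the nominal error rate. Nor does section 3.7 say that the time or group main effect will count as evidence. The abstract, Rh2, section 4 and the discussion all frame success as group 1 against the other two groups. Which contrast decides is commonly left to an analysis plan, so that silence is not held against the article. All of this stands. What remains is SO2, which plans intragroup comparisons, and Rh1, which lacks a comparator.

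The size of the within-arm problem is also open. A rate near 90% would be one assumed point, and the range in step 1 runs from 10% to 87%. The direction differs by outcome too: a growth-related rise in BMI would count as worsening, so a false improvement is most plausible for strength.

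Preferring ANCOVA is a matter of efficiency, since both estimators are unbiased under randomisation. A reader might turn the ratio (1+r)/2 into 10–25% fewer children for the same precision. That does not follow here, because it assumes independent children while six courses are randomised. A reader might also expect ANCOVA to cure unequal starting levels. Differences between intact courses may be stable, and a child-level baseline slope need not correct them better than a change score does.

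**Conclusion.** The point holds in a limited form. SO2 and Rh1 as worded leave room for a within-arm change to be reported as a programme effect. How often this would mislead depends on values the article does not give: about 18% to 87% for shared gains of 0.1 to 0.3 SD at r = 0.8, and 49% for 0.3 SD at r = 0.5, with 44 per arm. The time × group test is sound against shared change but gives up precision. The child-level loss is small if r is 0.8 to 0.9, as might be assumed for strength and anthropometry, and larger if r is near 0.5, as may be the case for self-reported screen time and sleep. Neither method deals with having two courses per arm.

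**What to change.** - In section 3.7, make the effect estimate the between-arm difference in post-test adjusted for the planned pre-test, with course accounted for as the randomised unit.
- Word Rh1 as group 1 versus control, and Rh2 as group 1 versus group 2 and group 1 versus control.
- Under SO2, report within-arm changes descriptively, without p-values.
- State that the time and group main effects are not evidence of benefit.

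The cost is rewording section 3.7, SO2 and the hypotheses. No new measurement is needed, because the pre-test is already scheduled in every arm. Accounting for course is more than wording: six courses in three arms leave 6 − 3 = 3 degrees of freedom between courses, so intervals may be wide. That follows from the design and applies equally to the present ANOVA if it is analysed as randomised.

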### 3.4. Randomization

An intentional sample will be carried out with randomization by course of the two selected establishments.

Each educational establishment has three fifth-grade courses each, with similar socio-educational characteristics for their level. The six courses will be randomized (24 subjects per course), of which two courses will represent intervention group 1, two courses will represent intervention group 2, and two courses will represent the control group.

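### Six whole courses are randomised, two per arm, but the planned repeated-measures ANOVA treats the children as independent, so its 5% test is anti-conservative if children within a course are at all alike

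*Protocol article*

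**What the plan says.** Section 3.4 (Randomization) makes the course the unit of allocation: "An intentional sample will be carried out with randomization by course of the two selected establishments". There are three fifth-grade courses in each of two schools, and "The six courses will be randomized (24 subjects per course), of which two courses will represent intervention group 1"; likewise, "two courses will represent intervention group 2, and two courses will represent the control group".

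Section 3.7 (Statistical Analysis) then names the method: "A 2-way repeated measures analysis of variance (ANOVA) will be used to determine the effects of the interventions". It lists the model's effects: "The effects of the model are the group (GE1; GE2; GC), the times (pre-test; post-test"), and the time × group interaction, followed by Bonferroni comparisons, Cohen's d and a threshold of p < 0.05. It mentions no course or school effect, cluster-robust variance or course-level summary.

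Section 2.2 (Participants) counts children only: "The sample size will be 144 children (48 for intervention group 1, 48 for the intervention group 2, and 48 for the control group"). It bases this on a calculation "considering α = 0.05, 1-β = 0.8, and an effect size of (ES) = 0.8", with no ICC or design effect. The limitations in the Discussion do not mention clustering.

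**The concern.** The repeated-measures structure covers the correlation between a child's pre-test and post-test. It does not cover the correlation between children in the same course. Such correlation is to be expected here: the strength sessions run in the classroom every school day, children in a course share teachers and timetable, and the Discussion itself names uneven teacher collaboration as a weakness. That is variation at course level, and the model leaves it out.

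If changes are positively correlated within courses, the standard error of a between-arm difference is too small. With only two courses per arm, an ordinary difference between courses could be reported as the benefit that section 4 expects for group 1. Bonferroni does not help, because each pairwise standard error is itself too small. The same applies to every outcome in section 3.6.

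**Working it through.** **Inputs.** 3 arms, 2 courses per arm, m = 24 children per course (section 3.4); 48 per arm, 144 in all (section 2.2); α = 0.05 (sections 2.2 and 3.7). The course-level ICC of the change score, ρ, is not in the article; 0.01 to 0.10 is an assumed range.

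**Step 1: the planned test.** With two time points, the time × group F-test equals a one-way ANOVA on change scores. Its error degrees of freedom are 144 − 3 = 141. At the level randomised they are 6 − 3 = 3.

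**Step 2: the plan's own figure.** At ρ = 0 the planned test does give its nominal 5% (simulated 0.050).

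**Step 3: expected mean squares under no effect** (total variance of change = 1).
- Between arms: D = 1 + (m − 1)ρ = 1 + 23ρ, the design effect.
- Planned error term, pooling 3 between-course and 138 within-course degrees of freedom: E = [3D + 138(1 − ρ)] / 141.

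The planned F is thus inflated by about D/E. The 5% critical value of F(2, 141) is 3.060. The true error rate is approximately P(F(2, 141) > x), with x = 3.060 × E/D. With 2 numerator degrees of freedom this has the closed form (1 + 2x/141)^(−70.5).

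Worked for ρ = 0.05: D = 2.15; E = (6.45 + 131.10)/141 = 0.9755; x = 3.060 × 0.9755/2.15 = 1.389; (1 + 2.777/141)^(−70.5) = 0.253.

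| Assumed ρ | D | Effective children per arm (48/D) | Type I error, formula | Type I error, simulated (200,000 trials) | Simulated F-test on six course means |
|---|---|---|---|---|---|
| 0 | 1.00 | 48.0 | 0.050 | 0.050 | 0.049 |
| 0.01 | 1.23 | 39.0 | 0.088 | 0.089 | 0.051 |
| 0.02 | 1.46 | 32.9 | 0.129 | 0.130 | 0.050 |
| 0.05 | 2.15 | 22.3 | 0.253 | 0.253 | 0.049 |
| 0.10 | 3.30 | 14.5 | 0.416 | 0.415 | 0.050 |

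A smaller simulation (20,000 trials) gave 0.126 at ρ = 0.02, hence 12–13% there. The chance of at least one significant Bonferroni pair in that run was 0.081, 0.114, 0.237 and 0.397 at ρ = 0.01, 0.02, 0.05 and 0.10.

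**Step 4: power of a valid analysis.** Take a pairwise contrast at d = 0.8, reading the stated effect size as Cohen's d in SDs of change; the article does not state the metric. The standard error is √(2D/48). With 3 error degrees of freedom the two-sided 5% critical t is 3.18, against 1.98 on 141. Power comes from the noncentral t with noncentrality 0.8/SE:
- ρ = 0: SE 0.204, noncentrality 3.92, power 0.74
- ρ = 0.01: SE 0.226, noncentrality 3.53, power 0.66
- ρ = 0.05: SE 0.299, noncentrality 2.67, power 0.45
- ρ = 0.10: SE 0.371, noncentrality 2.16, power 0.325 (about 0.32)

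These are before any multiplicity adjustment. The article plans on 0.80.

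**The case against.** The usual defence, that clustering is left to a fuller analysis plan, is weak here. The article names the method and lists its effects, so a later plan that added course would change the stated model. Other objections carry weight and limit the point.

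- **The size is conditional.** No ICC is given. At 0.01 the inflation is modest, at 0.10 it is severe, and the article does not say where this trial lies. It supports saying that a false positive could be reported, not that one will be.
- **Confidence intervals.** A reader might infer that planned intervals are wrong. Section 3.7 plans none. Intervals derived from this model would be too narrow (a nominal 95% pairwise interval covers about 81.5% at ICC 0.05), but that is a consequence and not something the plan states.
- **Re-randomisation.** A reader might infer that six courses can never give p < 0.05 without leaning wholly on a model. That goes too far. If allocation is unrestricted there are 15 × 6 = 90 labelled allocations. Under the sharp null of no effect in any arm, a test on the group 1 minus control difference can reach 2/90 = 0.022 two-sided. The floor of 1/15 applies to the global F statistic under unrestricted allocation. The floor of 1/3 (2/6) applies only to a pairwise test that holds the third arm's courses fixed.
- **School as a block.** Section 3.4 does not say that allocation is stratified by school. Without stratification, both courses of an arm may fall in one school, and a school term then partly confounds arm with school.
- **Shared sessions.** Section 3.5.1 has the recommendations for group 2 taught together with group 1. This may correlate courses across arms. The simulations assume six independent courses and do not model it, so the 5% shown for course means rests on that assumption.

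**Conclusion.** The mismatch between the unit of randomisation and the unit of analysis is real and must be fixed. It lies in what the article states: course-level allocation in section 3.4 and a child-level model, with its effects listed, in section 3.7. Nothing elsewhere corrects it.

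The direction is certain for any positive course-level ICC of the change score: the p < 0.05 test rejects too often. The size rests on an assumed ICC, 24 children per course and independent courses. At ICC 0.05 about one true null in four would be declared significant, and even at 0.01 the error rate nearly doubles. The article does not support stronger readings, such as a definite false finding, defective planned intervals or the impossibility of any significant randomisation test.

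**What to change.** In section 3.7, replace the child-level ANOVA with one of two analyses:

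- a course-level analysis: baseline-adjusted course means compared by arm on 3 error degrees of freedom; or
- a mixed model with arm fixed, baseline as covariate, a random course effect and small-sample degrees of freedom at cluster level.

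State in section 3.4 whether allocation is stratified by school, and add school as a block (2 error degrees of freedom) only if it is. Include course in the multiple-imputation model. Report estimates with intervals from the new model as the main result. If a re-randomisation test is added, specify its statistic and reference set in advance, since these determine the smallest attainable p-value.

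Treatment and data collection do not change, but the cost goes beyond rewording. Intervals widen, and pairwise power at d = 0.8 falls to the values in step 4, below the stated 80%. Section 2.2 should restate power with a named ICC range, and the limitations should list the two courses per arm. Extra children in the same courses cannot replace extra courses. With 22 children per course, a two-arm t-test on course means would need about 3 courses per arm at ICC 0.01–0.02, 4 at 0.05 and 5 at 0.10 for 80% power. If courses cannot be added, the trial should be presented as low-powered and its estimates read accordingly.

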## 4. Expected Results

It is expected that the combined exercise program of muscle strength, lifestyles, and nutritional education (group 1) will present better results in terms of improving physical condition, cardiovascular risk, and healthy lifestyle compared to group 2, with only nutritional and lifestyle recommendations, and to the control group.

## 5. Discussion

The objective of this project is to show the efficacy of a multicomponent program of strength exercises + nutritional recommendations, sleep, and use of screens related to cardiovascular risk and strength in schoolchildren aged 10–12 years in educational centers of Chile with extremely cold weather.

It is expected that the group in which the strength interventions and lifestyle recommendations are applied will obtain significant results in terms of strength, decreased cardiovascular risk, improvements in sleep habits, and fewer hours of screen use compared to the group that will carry out only the nutritional and lifestyle recommendations and the control group that carries out their usual school day.

Regarding muscle strength and cardiovascular risk, overweight children who increase their muscle strength decrease cardiometabolic risk, unlike overweight children who do not increase their muscle strength [32,69,70,71]. Muscle strength and nutritional status can be assessed through the WtHr and BMI, which are predictors of cardiovascular risk in the prepubertal stage [62,72,73]. Strength is a significant indicator of health, which can be assessed by handgrip strength for the upper limbs and long jump for the lower limbs, the latter being the most relevant because schoolchildren develop this kind of ability at an earlier age [74]. On the other hand, an increase in muscle mass and strength encourages physical activity, reducing sedentary lifestyle and improving anthropometric indices [75,76], which leads to better physical self-perception, improvement in self-esteem, and increased levels of movement [77,78]. Along the same lines, a higher level of muscle strength boosts daily energy expenditure and lipid oxidation, resulting in better anthropometric measurements, better nutritional status [79,80], and a decrease in cardiovascular risk [80,81], a condition opposite to children with lower levels of muscle strength associated with worse cardiorespiratory conditions [82].

*Intervention characteristics:*

The intervention will be carried out for six months, allowing relevant results maintaining high adherence to be achieved and not suffering losses in the sample [83]. The adherence may also be related to the participation of teachers at the educational center and parents/guardians because the intervention includes healthy lifestyle education at home and at the school center [84]. Another characteristic of the project is the implementation of the intervention in the educational center, providing effectiveness and little sample loss, according to previous studies [8]. The combined intervention of strength + nutritional recommendations should include lifestyle changes [85] to ensure that long-term effects are maintained [86]. The beneficial effects of the interventions that combine components [3] have been documented in both the short term (≤6 months) and long term (≥12 months) [85,87], as reported in a systematic review where interventions lasting six months or less presented significant effects in 77% of the cases. According to the components addressed, the modalities that showed the highest effectiveness were physical activity, recreational activities (100%), a nutrition and diet program (100%), education (100%), and behavioral therapy (65%) [13].

*Limitations and strengths:*

This paper presents some weaknesses that need to be expressed. The first corresponds to the time for carrying out the intervention because the schedules of educational centers are rigid and structured and could be affected by the integration of an intervention model inside the classroom within the school day [26]. Another weakness could be the heterogeneous level of collaboration among teachers for using traditional class time.

However, the main strengths of the intervention correspond to carrying out the intervention within school hours [88], which can guarantee that all children and adolescents have the opportunity to participate, eliminating access barriers, such as distance and/or economic resources for transfers. Another strength of carrying out the intervention within the school day is the support of the teachers, who can play an active role in monitoring the intervention by encouraging the creation of healthy habits from an early age [28,29].

*Impact of the intervention:*

This type of intervention that combines strength exercises and nutritional and lifestyle recommendations can generate short-, medium-, and long-term health benefits for children and adolescents, such as improved physical condition, motor skills, and concentration; decreased anxiety; and the adoption of healthy eating and lifestyle habits [89,90]. This can have a positive impact on their academic performance, cognitive function, and general health status [91], including the prevention of chronic non-communicable diseases, such as obesity, type 2 diabetes, and cardiovascular diseases [92].

These types of interventions become relevant in the current context where children and adolescents increased their obesity rates as a result of an unhealthy lifestyle added to the decrease in physical activity, a consequence of the COVID-19 pandemic [93].

*Practical applications:*

This intervention within the school day can be incorporated into the school curriculum as other countries have done [94,95]. Strength exercises can be included daily at the beginning of the school day, and the recommendations of healthy lifestyle and nutrition habits within the curriculum of all classes [96]. This work plan can be carried out with the use of mobile applications, which offer personalized exercise routines with different types of levels and objectives according to their achievements, and can also be in a playful format to further attract children and adolescents [97,98]. In addition, this type of intervention can promote the creation of a healthy school environment [10], which consists of public policies that restrict the sale of unhealthy foods within educational establishments. Also, it can promote nutrition and daily physical activity habits within the establishment by doing sports, dances, and exercises and contacting places that deliver healthy food [99,100,101]. Finally, this intervention can coordinate with local institutions the realization of extracurricular activities that present sports and physical activity programs [102].

